## **7.5 Monitoring procedures**

Persons with direct access in accordance with the current legislative and regulatory requirements, in particular articles L.1121-3 and R.5121-13 of the "Code de la Santé Publique (CSP)" (*French Health Law*; for example, investigators, quality control personnel, monitors, clinical research associates, auditors and all persons called upon to collaborate in the study) take all necessary precautions to ensure the confidentiality of information relating to the investigational product(s)/material(s), the study, the persons taking part in the study and in particular their identity and the results obtained. The data collected by these people during quality controls or audits is then rendered anonymous.

The research will be supervised in accordance with the standard operating procedures of the sponsor or CRO.

The research will be conducted in the investigating centres and patients will be managed in accordance with the Declaration of Helsinki and current Good Clinical Practice.

The level of monitoring will involve the following provisions:

- scientific commitment to good practice;
- initiation visit to each centre by the CRAs representing the sponsor prior to inclusion, to set up the protocol and get to know the people involved in the research.
- consent of subjects included;
- reporting of SAEs and new evidence;
- study data monitoring;
- close-out visit to each centre by the CRAs representing the sponsor: recovery of data from the CRFs, report to the pharmacy, study documentation, archiving.

### **7.5.1 IJL investigation site set-up:**

At the start of the study, the monitor will meet with the investigating team during an initiation visit to set up the study. The monitor will ensure:

- that there is no ambiguity and that the scientific protocol and its appendices have been fully understood (especially the CRF),
- that the procedures specific to the study have been put in place (data collection, etc.).

The monitor will provide the access codes for the e-CRF.

The main aspects of the study will be discussed in detail with the investigator and/or his or her team to ensure that there are no unresolved problems concerning the protocol, administrative issues or the logistics to conduct the study.

#### 7.5.2 Investigation site monitoring:

During the study, the monitor will visit the IJL investigation site (20 visits during the study); he or she will also be available by telephone to answer any questions or resolve any difficulties relating to the study. During these visits, the monitor will ensure that the study is conducted adequately and will carry out quality control on the data and their records. The monitor will also ensure that the protocol is complied with.

The investigator must make available to the monitor all source data relating to the medical files of the patients included and all duly signed informed consents.

The monitor must have direct access to the source documents (original documents, data and records). A specific login and password for the monitor will be created for the duration of the study, and he or she will only have access to data relating to patients included in the study once informed consent has been signed. This direct access includes permission to examine, analyse, verify and reproduce any document(s) and report(s) deemed important for the evaluation of the clinical study.

The data entered in the electronic CRF will be checked against the source documents by the monitor during his or her visits.

Each monitoring visit will give rise to a monitoring visit report in which the progress of the study and any difficulties identified will be indicated.

#### 7.5.3 Investigation site closure:

At the end of the study, a visit to the IJL site will make it possible to check where the study material will be archived (documents, product(s)/material(s), etc.) and that the investigator has taken the necessary steps to close the site.

### 7.6 Study stopping rules

The sponsor or the Competent Authority (ANSM) may temporarily or definitively interrupt all or part of the study in the following situations:

- first, in the event of unexpected serious adverse effect (USAE) requiring a reassessment of the risk/benefit ratio of the research
- similarly, unexpected events or new information, in the light of which the objectives of the research or clinical programme will unlikely to be achieved, may lead the sponsor or the Competent Authority (ANSM) to interrupt the study prematurely
- the sponsor reserves the right to suspend inclusions definitively, at any time, if it appears that the inclusion objectives are not being met.

In the event of premature termination of the research, the decision and justification are sent by the sponsor to the Competent Authority and the Research Ethics Committee within 15 days.

### **7.7 Scientific expert**

[name], Head of the Paediatric Non-invasive Ventilation and Sleep unit at Necker-Enfants Malades Hospital, is the study's scientific director. The scientific director and the coordinating investigator are involved in drafting the research protocol, the statistical analysis plan and the clinical report for the study. Where appropriate, they may propose or be consulted about any substantial changes to be made to the study. They will also be consulted during data validation before the study database is frozen.

## 8. VIGILANCE

### 8.1 Definitions

The definitions relating to the vigilance of a clinical study are described in article R1123-46 of the CSP.

An adverse event (AE) is any untoward medical occurrence in a person participating in human research, and which does not necessarily have a causal relationship with the research or product administered in the framework of the research.

In the case of an HPS study, an adverse effect is defined as any AE related to the research.

Any AE considered by either the investigator or the sponsor to have a scientifically reasonable causal relationship with the research is referred to as an adverse effect. This generally means that there is evidence or an argument to suggest, on a scientific level, a causal relationship between the untoward reaction observed and the research. The AE due to the research may be related, for example, to the procedures, methods, acts performed or products being studied or used for the needs of the research.

A serious adverse event (SAE) is any event that:

- Leads to death
- Is life-threatening for the person participating in the research
- Requires hospitalisation or prolongation of existing hospitalisation
- Causes significant or persistent incapacity or substantial disruption of the ability to conduct normal life functions
- Results in a congenital anomaly or birth defect
- May be life-threatening for the subject or require intervention to avoid developing into one of the above criteria

An unexpected adverse effect is any adverse effect whose nature, severity or course is not consistent with the product information, procedures and methods used during the research.

Possible adverse effects are those described in the instructions for use for the various devices:

- the gel used for the measuring sensors may cause a reaction in the event of an allergy to one of the ingredients,
- the surgical tape used to attach the sensor cables may cause a reaction in the event of an allergy to one of its components,
- the ear sensor may cause discomfort due to a rise in temperature.

Any adverse effects and SAEs that may occur during the home test will be reported in the e-CRF and to the sponsor.

As part of the protocol, it is important to monitor ENT and cardiopulmonary complications, since ENT abnormalities are risk factors for sleep apnoea. Moreover, there are two aspects to the treatment of sleep apnoea syndrome: ENT (tonsillectomy, adenoidectomy) and respiratory (CPAP)

As the primary endpoint involves tests to assess neurocognitive and behavioural development, we will also monitor all neurological events, which are confounding factors in children's intellectual disability and may influence the primary endpoint.

AEs and serious AEs linked to the ENT (otitis, angina, rhinitis, pneumopathy, other), neurological and cardiopulmonary systems will also be reported in the e-CRF and to the sponsor. Initiating antibiotic treatment or hearing aid fittings should also be recorded.

## **8.2 The role of investigators**

The CRN will record in the e-CRF all AEs (related to the protocol, related to ENT, neurological and cardiopulmonary systems) collected during bimonthly telephone calls or via spontaneous contacts with the parents of children taking part in the study. Investigators must validate these AEs. At each visit as part of the patient's usual follow-up, the investigators must also record in the e-CRF all AEs (related to the protocol, related to ENT, neurological and cardiopulmonary systems) occurring in patients of which they have direct knowledge, from the date of signature of the consent by the legal representatives to the end of follow-up. If a patient is withdrawn prematurely from the study and experiences a serious adverse effect (protocol-related, related to ENT, neurological or cardiopulmonary system), the patient should be monitored until the event is resolved.

Investigators assess the severity and causality of all AEs.

The investigators report to the sponsor without delay only SAEs related to the protocol, related to ENT, neurological and cardiopulmonary systems.

As cardiac surgery and orchidopexy are frequent in patients with DS and have no link with the protocol, they will not be recorded in the e-CRF.

Hospitalisations scheduled before the patient enters the study will only be recorded in the e-CRF if they are related to the ENT, neurological or cardiopulmonary systems.

Hospitalisations for PSG, surgical procedures for the treatment of OSA, tonsillectomy and adenoidectomy, and the trans-tympanic aerators installation will be recorded in the e-CRF.

In accordance with current legislation, the investigator will report serious AEs and adverse reactions to the French vigilance systems (pharmacovigilance, medical devices vigilance, etc.) applicable to each product (drugs, IVDMDs, etc).

In accordance with current regulations, new evidence will be reported without delay to the Regional Pharmacovigilance Centres (<https://www.pharmacovigilance-iledefrance.fr/>) for drugs and to the medical devices vigilance for medical devices.

An SAE associated with care (SAEC) is an unexpected event with regard to the person's health status, the consequences of which are:

- the probable occurrence of a permanent functional impairment
- life-threatening conditions
- death
- Investigators will report these SAECs via the [https://signalement.social-sante.gouv.fr/psig\\_ihm\\_utilisateurs/index.html#/choixSignalementPS](https://signalement.social-sante.gouv.fr/psig_ihm_utilisateurs/index.html#/choixSignalementPS)
- He or she will also declare any new evidence (any new safety data that may lead to a reassessment of the risk/benefit ratio of the study, or that may be sufficient to consider changes to the documents relating to the study)

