### **8.3 The role of the sponsor**

The sponsor is responsible for the ongoing evaluation of the safety of the study.

The sponsor will receive an e-mail notification in real time for each SAE form completed by the investigator as part of the protocol.

During monitoring visits, the sponsor will ensure that the investigator has made the required reporting.

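### For an SAE outside three organ systems and not during a home PSG, section 8.2 lets the investigator's causality opinion alone decide whether the sponsor is told, deaths included

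*Protocol*

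**What the plan says.** **Definitions.** Protocol section 8.1 lists the criteria that make an event serious. The first is "Leads to death", and none is limited to a body system or a cause. The same section classes as an adverse effect "Any AE considered by either the investigator or the sponsor to have a scientifically reasonable causal relationship with the research".

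**Reporting statements in 8.1.** For the study procedure: "Any adverse effects and SAEs that may occur during the home test will be reported in the e-CRF and to the sponsor". For the organ systems of interest, AEs and serious AEs in the ENT, "neurological and cardiopulmonary systems will also be reported in the e-CRF and to the sponsor". Neither statement depends on the investigator's view of causality.

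**Recording and reporting rules in 8.2.** The nurse and the investigators enter in the e-CRF "all AEs (related to the protocol, related to ENT, neurological and cardiopulmonary systems"). For onward reporting: "The investigators report to the sponsor without delay only SAEs related to the protocol, related to ENT, neurological and cardiopulmonary systems".

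**Sponsor's duties.** Section 8.3 says: "The sponsor is responsible for the ongoing evaluation of the safety of the study". The sponsor is alerted by e-mail whenever the investigator completes an SAE form. In section 7.6, the first ground for interrupting the study arises "in the event of unexpected serious adverse effect (USAE) requiring a reassessment of the risk/benefit ratio of the research".

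**Nurse calls.** Section 7.3 has the nurse collect adverse events of any kind every two months. Section 7.3.13 narrows this to protocol-related events linked to the three systems.

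**The concern.** Section 8.1 sets up a two-party causality judgement: an event counts as related if either party thinks so. That needs the second party to know of the event. Outside the three systems, section 8.2 makes the report itself depend on the first party's answer, so an investigator's opinion of unrelated is final because the sponsor is not required to be told.

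A second opinion is worth having here. The study is open-label, and its two investigating centres are also those that organise the screening and deliver the OSA treatment. The children in the Screened Group enter at 0 to 6 months of age and stay until 36 months. Section 9.3 plans a safety analysis on all included patients, and under the present rule a count of all SAEs in that population cannot be complete.

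**Working it through.** No formula or stated figure is involved. The check is to apply sections 8.1 to 8.3 to each kind of SAE and see whether it reaches the sponsor. I read the list in 8.2 as alternatives (protocol-related, or in one of the systems), which agrees with 8.1. Requiring both conditions, as 7.3.13 words it, would widen the gap.

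| SAE | Investigator's opinion | Reaches the sponsor as an SAE? |
|---|---|---|
| (a) In the ENT, neurological or cardiopulmonary systems | Any | Yes (8.1, 8.2), apart from the named surgery exemptions in 8.2 |
| (b) During the home PSG, any system | Any | Yes under 8.1, but the word *only* in 8.2 would exclude some of these |
| (c) Other system, not during a home PSG | Related | Yes (8.2) |
| (d) Other system, not during a home PSG | Not related | No report and no e-CRF entry required (8.2) |

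The sponsor's causality judgement can operate in rows (a) to (c). In row (d) it cannot, and row (d) is where it could change the classification of an event outside the three systems.

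Next, does anything else in the protocol close row (d)?

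- **SAE alert (8.3).** It is triggered by a completed SAE form, and 8.2 does not call for one in row (d). The sponsor's check at monitoring visits is of the required reporting, which is the filtered set.
- **Premature withdrawal (7.3.14).** Date and reason go in the e-CRF. Death is not a listed reason, so it would fall under the open category. This covers only departures before the 3-year visit, and it is not an SAE report.
- **Care-associated SAEs (8.2).** These go to a national portal. The sponsor is not named as a recipient.
- **Nurse calls (7.3).** The wider wording there conflicts with 7.3.13 and with 8.2. Even if it prevailed, it would give collection of events, not SAE reporting.
- **A timing reading of 8.2.** One could take *only* as restricting immediate reporting, with other SAEs following later. No slower route is given, and e-CRF recording has the same filter.

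**Size.** The exposure of the Screened Group follows from the design: entry at 0 to 6 months and follow-up to 36 months give 2.5 to 3 years per child, and 40 × 2.5 = 100 to 40 × 3 = 120 child-years before attrition. A count of row (d) events would also need an SAE rate outside the three systems and the share judged unrelated. The protocol gives neither, so no count can be derived.

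**The case against.** The best defence is that the restriction is deliberate. The study is minimal-risk and without drug. The foreseen effects are gel or tape allergy and discomfort from the ear sensor. Section 8.1 explains the choice of systems: ENT abnormalities are risk factors for OSA, treatment is ENT or respiratory, and neurological events could confound the primary endpoint. The either-party wording is a definition and does not expressly promise sponsor review of every event. Those reasons do explain collecting extra events in three systems. They give no ground for withholding other serious events.

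Three stronger readings are tempting, and the protocol does not support them:

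- *The sponsor's causality review fails altogether.* It does not. It works for SAEs in the three systems and for all SAEs during the home test as 8.1 has it, and events of any system that the investigator calls related are reported.
- *Deaths from other causes leave no trace.* A death before the 3-year visit is entered as a withdrawal with date and reason. Treatments are recorded, the start of antibiotics among them. Section 8.2 has investigators declare new safety data that bear on risk and benefit. Section 7.5.2 gives the monitor direct source access over 20 visits. None of these is an SAE report, but together they rule out saying that the sponsor could never learn of such an event.
- *The first stopping ground is disabled.* An adverse effect is research-related by definition, and SAEs that the investigator calls related are reported whatever the system. What is lost is only an event that the sponsor might have judged related when the investigator did not. Section 7.6 also has a separate ground for unexpected events or new information.

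It is also fair to say that tasks are divided. Necker reads the PSGs and treats OSA, while the nurse and the annual consultations are at the IJL. The independence argument is therefore about the two centres together and should not be pressed as if one person did everything.

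**Conclusion.** The point holds in a limited form. There is one class of SAE, row (d), for which section 8.2 requires no report to the sponsor and 8.1 gives the sponsor a judgement that it then cannot make. Deaths are included. Two textual conflicts sit beside it: 8.1 against 8.2 on SAEs during the home test, and 7.3 against 7.3.13 and 8.2 on what the nurse collects.

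The conclusion rests on the text alone and needs no event rate. A reader might want a number: an assumed 0.1 to 0.3 SAEs per child-year outside the three systems would give 100 × 0.1 = 10 to 120 × 0.3 = 36 events. Nothing in the protocol supports that rate, and some of those events would still be reported under rows (b) and (c), so the range should not be quoted as the size of the gap. The sample size and the primary analysis are not affected. This is a cheap improvement in safety oversight that the sponsor should make.

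**What to change.** In section 8.2, replace the restricted reporting sentence with a rule that every death and every SAE from consent to the end of follow-up, whatever the organ system, is recorded on the existing SAE form and sent to the sponsor with the investigator's causality opinion, so that the sponsor can form its own. Keep the organ-system filter for non-serious AEs. Keep the exemptions that 8.2 names, for non-fatal planned procedures only. Then reconcile 7.3, 7.3.13, 8.1 and 8.2 so that they state one scope for collection, one for recording and one for reporting.

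The cost is small. The SAE form already has boxes for death and for an unrelated event, and the e-mail alert already exists. The downside is some additional reports of unrelated SAEs in a cohort of 80. If the change is treated as a substantial amendment, section 10.3 requires ethics committee approval first.

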### **8.3 The role of the sponsor**

The sponsor is responsible for the ongoing evaluation of the safety of the study.

The sponsor will receive an e-mail notification in real time for each SAE form completed by the investigator as part of the protocol.

During monitoring visits, the sponsor will ensure that the investigator has made the required reporting.

## **9. STATISTICAL ANALYSIS**

### **9.1 Sample size calculation**

Sample size calculation is based on the expected results of the Griffiths III neurocognitive assessment test. The expected difference between the mean score of the *Screened Group* and the mean score of the *Standard Care Group* was defined empirically by the experts and set at 8 points. Ellis et al. report the results of a clinical study in children with DS in whom Griffiths III was conducted on subjects between the ages of 18 and 25 months. The standard deviation used to calculate the sample size was used for the present study. Although the version of the GMDS used in the Ellis et al. study is an earlier version than the one to be used in the present study, the experts considered that the variance should not be significantly impacted. A standard deviation of 11.55 was therefore used.

By setting the type I error at 5% and the type II error risk at 20%, 34 children must be included in each of the groups in order to be able to demonstrate a difference of at least 8 points between the two groups with a power of 80%. Assuming an attrition rate of 15% due to lost to follow-up or missing data, 40 patients per group should be included, for a total of 80 children. This sample size is compatible with the inclusion capacity based on incidence of DS and also the technical constraints imposed in performing PSG.

### **9.2 Data management / data validation**

A data management plan will be drawn up by CLINACT and submitted to the sponsor for approval. This will contain, among other things, the list of data validation tests. In the event of inconsistent data, a data clarification form will be generated and will have to be addressed by the investigator during electronic data entry. Decisions about pending inconsistent data at the end of the study will be made at the review meeting before the database is frozen. The information will be encrypted and unique to each instance.

### **9.3 Statistical analysis**

The statistical analysis will be carried out by CLINACT using SAS software version 9.2 or later. Statistical tests will be considered significant if the level of significance is less than 5% for all analyses. Comparisons will be bilateral.

The main statistical analysis will focus on the "intent-to-treat" (ITT) population. A second analysis will be carried out on the "per protocol" (PP) population in order to confirm the results of the analyses of the primary endpoint.

A statistical analysis plan will be drawn up once the protocol has been approved. This document will present an exhaustive list of the analyses that will be carried out and the statistical methods that will be applied. This document will be used as a reference for statistical analyses.

There will be a single analysis at the end of the study (final analysis).  
Missing data at the time of analysis will not be replaced and will be considered as such.  
Patients included, with an assessment of the primary endpoint, will be included in the "intent-to-treat" (ITT) population.  
ITT patients without major protocol deviations will be included in the "per protocol" (PP) population.  
These deviations will be defined before the database is frozen: for example, failure to comply with the protocol or the presence of an exclusion criterion.  
The safety analysis will be carried out on the Safety population (all patients included).

